### Statistical analysis

Statistical analyses will be supervised by a skilled statistician and performed with MATLAB and STATA. We will analyze all randomized participants for whom the T1 assessment of the primary outcome and at least one training session are available (i.e., the “intention-to-treat” principle). The interim analysis, including 30 participants, will guide the final statistical methodology. The short-term efficacy of the intervention will be analyzed using the changes between T1 and T0. As the null hypothesis, we postulate that the change before and after the intervention (T1–T0) will not differ between the two groups. We will use simple comparison tests (*t* tests) and multiple regressions; in this case, intervention intensity (number of training sessions), disease etiology, and age will be used as covariates. Furthermore, we will longitudinally analyze (linear growth model) the gait parameters recorded in each gait training session; we hypothesize (H0) that the change over time will be equivalent between groups. We will also assess the difference between groups for the outcomes that are measured at T2 (3-month follow-up). Finally, as a subgroup analysis, we plan to analyze stroke survivors, TBI, and SCI patients separately.

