### Setting

The study takes place in the Clinique Romande de Réadaptation (CRR, Sion, Switzerland). This clinic offers 145 beds and is one of the main rehabilitation centers in western Switzerland (with its 2.1 million inhabitants). Because of its affiliation with the accident insurance company SUVA, the CRR is a common referral center for traumatic injuries, especially for SCIs. The overall objective of the CRR’s therapeutic program is to take care of patients through a multidisciplinary approach to improve their quality of life, functional status, and chance of returning to work. The number of hospitalized patients at the CRR is about 1200 per year, with an average stay of 40 days. Recruitment for this study began in June 2016. A 2-year framework is planned for the study, with possible adjustments according to the results of the interim analyses (see below).

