### Participants

Study participants will be recruited from among the inpatients admitted for neurorehabilitation at the CRR. Selection of the inclusion criteria was guided by the rationale of reflecting the prevailing choice in neurorehabilitation clinics of specific therapies that are tailored to patients’ needs. A summary of the inclusion/exclusion criteria is shown in Table 2. Potential candidates will be monitored during their first 3 weeks after admission (Fig. 1). Motor functions will be assessed by a skilled neurologist, who will evaluate the need for gait rehabilitation. If and when the candidate is able to walk during a 2-min test, a final decision for inclusion will be made. Those candidates who do not exhibit sufficient walking capacities after 3 weeks will be excluded.

**Table 2 Tab2:** Inclusion and exclusion criteria

Inclusion criteria	Exclusion criteria
Patient with stroke, traumatic brain injury, or spinal cord injury in acute to subacute phase	Age <18 years
First stage of rehabilitation (<40 days after incident)	Clinically significant concomitant disease states (e.g., cardiovascular disease) that may threaten the patient’s health in case of sustained exercise
Need for gait rehabilitation because of at least one of the following conditions: • Paresis of the lower extremities • Severe balance disorders • No walking at admission	Concomitant gait disorders induced by acute to subacute musculoskeletal injuries (e.g., fracture of the lower extremities)
Ability to walk for 2 min without aid or with minimal aid, namely: • With the help of one person, or: • With walking aid (cane, walker)	Severe preexistent gait disorders that deeply affect walking abilities and gait pattern, either because of musculoskeletal (e.g., severe osteoarthritis) or neurological (e.g., Parkinson’s disease) etiologies
Informed consent as documented by signature	Severe noncorrected visual impairment.
	Inability to follow the procedures of the study, e.g., because of language problems, psychological disorders, dementia, etc.

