### Assignment of interventions and blinding

Assignment is effected by a block randomization procedure with varying block size, implemented by independent researchers not affiliated with the GASPAR study. The STATA package RALLOC [30] is used to generate the sequences. The ratio between the intervention and the control group is 2:1; this facilitates recruitment [31] and provides a broader range of information and experience about the AR program. In addition, stratification is made according to the type of injury: stroke patients, TBI patients, and SCI patients. This procedure ensures the comparator and treatment groups to be populated by patients with comparable disease etiologies and thus facilitates interpretation of the results. Sequentially numbered, opaque, sealed envelopes are used to conceal the allocation. Informed consent is obtained by the principal investigator or his/her delegate. Inclusion is confirmed by the referring neurologist. After baseline assessments are taken (T0), the sealed envelope is opened to allocate the participant.

Given the nature of the intervention and its clinical setting, masking is not possible. However, the use of an objective measure as the primary outcome minimizes the risk of bias.

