## Discussion

Particular attention has been paid to the study’s pragmatic design, to ensure that it guarantees high generalizability and yields useful findings. We evaluated protocol design according to the rating grid proposed by the PRagmatic Explanatory Continuum Indicator Summary (PRECIS)-2 guidelines [28] (Table 4). The average score among the nine PRECIS domains is 4.33, which indicates a rather pragmatic protocol. Issues that tend to lower the score are: (1) the focus on a subpopulation of neurologic patients, and (2) the fact that the trial takes place in a single center with some particularities (high-income country, over-representation of traumatic patients).

**Table 4 Tab4:** PRagmatic Explanatory Continuum Indicator Summary (PRECIS-2) scores of trial domains

	Domain	Score	Rationale
1	Eligibility criteria	3	P: inclusion of patients with gait disorders whatever the etiology
			E: focus on acute to subacute patients in first phase of rehabilitation
2	Recruitment path	4	P: recruitment of participants through usual clinical care at admission
			E: specific procedures to assess eligibility (3 weeks of monitoring)
3	Setting	3	P: study takes place in a neurorehabilitation unit
			E: single-center trial in a high-income country
4	Organization intervention	5	P: resources, provider expertise, and organization of care delivery in both study arms are similar to usual care
5	Flexibility of experimental intervention: delivery	5	P: identical flexibility to usual care
6	Flexibility of experimental intervention: adherence	5	P: no more than usual encouragement to adhere to the intervention
7	Follow-up	4	P: assessment of outcomes through usual clinical care
			E: specific procedure for follow-up after discharge
8	Outcome	5	P: outcomes are of obvious importance to participants and caregivers
9	Analysis	5	P: intention-to-treat analysis with all available data

Score: 1 Very explanatory; 2 Rather explanatory; 3 Equally pragmatic/explanatory; 4 Rather pragmatic; 5 Very pragmatic. *P* pragmatic, *E* explanatory

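### The set labelled intention-to-treat requires a T1 test and at least one training session, so it is a modified-ITT, complete-case set selected after allocation

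*Protocol article*

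**What the plan says.** The Statistical analysis section defines the set: "We will analyze all randomized participants for whom the T1 assessment of the primary outcome and at least one training session are available". The same sentence glosses this as "i.e., the “intention-to-treat” principle". Table 4 in the Discussion gives the rationale for the Analysis domain, scored 5, as "P: intention-to-treat analysis with all available data".

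The section on assignment and blinding fixes the order of events: "After baseline assessments are taken (T0), the sealed envelope is opened to allocate the participant". It also says: "Given the nature of the intervention and its clinical setting, masking is not possible". The primary contrast is the change from T0 to T1, compared between groups by t tests and multiple regression.

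**The concern.** Intention-to-treat means that every randomised participant counts in the arm assigned. Here a participant enters the analysis only after passing two filters, a first training session and a T1 walk test. Both lie after allocation, when patient and staff know the arm. The article defends the lack of masking by the objectivity of the primary measure. That protects against biased measurement, but not against selection of who is measured.

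Two things are at stake. The trial would report as intention-to-treat a result that is not one. And if the reasons for missing T1 differ between arms and are tied to recovery, the comparison loses the protection of randomisation. The article itself names one possible arm-specific reason: under Safety and confidentiality it says that dizziness or vertigo with augmented reality (AR) cannot be excluded.

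**Working it through.** **1. The plan's own figures.** The planned total is 70–100. The etiology counts per year add to 20 + 10 + 5 = 35 and 25 + 15 + 10 = 50. Over two years that is 70 and 100, as stated. This figure is not in dispute. No SD, effect size or attrition rate is given, so any size of bias rests on assumptions.

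**2. Who is in and who is out under the rule.**

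| Patient after allocation | In the stated set? | In an ITT set? |
|---|---|---|
| At least one session, T1 measured | yes | yes |
| Stops training after one or more sessions, T1 measured | yes | yes |
| No session, T1 measured | no | yes, with the observed value |
| T1 missing, with or without sessions | no | yes, through a missing-data method |

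The third row is an avoidable loss of observed data. The fourth is a missing-data problem that the rule settles by deletion.

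**3. Possible bias (all inputs assumed).** Let d be the proportion excluded in an arm. Let Δ be the shortfall in change, in SD units, of excluded against analysed patients. The full-arm mean is (1 − d)·m + d·(m − Δ) = m − dΔ, where m is the analysed mean. So the analysed mean is too high by dΔ. With the same Δ in both arms:

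bias = (d_AR − d_C) × Δ

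Type I error, taking no true difference, 2:1 allocation, a two-sided 5% test and the normal approximation:

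Φ(−1.96 + bias/se) + Φ(−1.96 − bias/se), with se = √(1/n_AR + 1/n_C) and n the analysed numbers.

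Example with 100 randomised, loss 25% versus 5%, Δ = 1:
- n_AR = 66.67 × 0.75 = 50 and n_C = 33.33 × 0.95 = 31.67
- se = √(0.0200 + 0.0316) = 0.227
- bias = 0.20 × 1 = 0.20, so bias/se = 0.881
- type I error = 0.1402 + 0.0023 = 0.1425

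| Loss AR / control | Δ (SD) | Bias (SD) | Type I error, N = 70 | Type I error, N = 100 |
|---|---|---|---|---|
| 10% / 10% | 0.5 or 1.0 | 0 | 0.0500 | 0.0500 |
| 15% / 5% | 0.5 | 0.05 | 0.0541 | 0.0558 |
| 15% / 5% | 1.0 | 0.10 | 0.0664 | 0.0736 |
| 25% / 5% | 1.0 | 0.20 | 0.1141 | 0.1425 |

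The sign follows Δ. If the lost patients are poor responders, excess loss in the AR arm favours AR. If they are fast recoverers who leave early, Δ is negative and the bias runs the other way.

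**4. A worst case.** Suppose the AR arm alone loses exactly its worst 10% of responders. The mean of the rest rises by φ(z)/(1 − q) = 0.1755/0.90 = 0.195 SD. With about 85 randomised (57:28), 51 and 28 are analysed, and a two-sided t test rejects in about 13% of trials. In the terms of step 3 this is a loss difference of 0.10 with Δ = 0.195/0.10 = 1.95 SD, well beyond the table.

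**5. The timetable.** The Participants section says: "Potential candidates will be monitored during their first 3 weeks after admission". Table 1 places screening at weeks −3 to −1 and T1 in week 5, after four weeks of training. That is 7 + 28 = 35 to 21 + 28 = 49 days before T1. The Setting section describes about 1200 admissions a year "with an average stay of 40 days". Eligible patients number 35–50 a year, that is 35/1200 = 2.9% to 50/1200 = 4.2% of admissions, so the clinic-wide mean says little about their stay.

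**The case against.** The case on the other side is substantial, and much of it stands.

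- **A reader might infer that the rule removes everyone who stops for fatigue or dizziness.** It does not. One session plus a T1 test keeps a patient in. The article also provides for reduced training in tired patients, and T1 is done as part of usual care.
- **A reader might infer from 49 days against a 40-day stay that missing T1 is likely.** The 40 days is a mean over all admissions, and 21 days is the longest monitoring period, since inclusion is decided as soon as the patient can walk for two minutes. The comparison is only a pointer to possible missing T1.
- **A reader might take 13% as the expected false-positive rate.** It assumes loss in one arm only, and only of its worst responders. The article gives no attrition figure. Differential loss is not shown: both arms use the same treadmills at comparable frequency and intensity, and the article says that dizziness from AR has never been reported.
- **How missing T1 is modelled may be left to an analysis plan that is not shown.** That is fair, and its absence here is not the point. But the exclusion rule and its label are positive statements in this document, and a later plan would have to contradict them to put them right.
- **The rule is stated openly, and Table 4 adds that available data are used.** So readers can see who is analysed. The label is still wrong. Whether a score of 5 is wrong depends on guidance not at hand, and it is not challenged here.

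**Conclusion.** The point holds as a wrong label and a badly fixed analysis set. The set is modified ITT / complete case, and Table 4 repeats the error. Excluding untrained patients who have a valid T1 serves no purpose. Excluding patients without T1 can bias the primary comparison, but only if loss, or its relation to outcome, differs between arms. If both are equal, the bias is zero.

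Size and direction cannot be determined from the document. The figures of 5%, about 5.4–7.4% and about 11–14% rest on assumed loss rates and shortfalls, a common Δ and a normal approximation. The 13% figure is a worst-case illustration. The documents do not support a claim that the result will be biased or that it will be biased in favour of AR.

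**What to change.** - Define the primary set as all randomised participants, in the arm assigned, and remove the session-attendance condition.
- Seek the T1 test from everyone, whatever amount of training was completed.
- Handle missing T1 with a T0/T1 mixed model, or with multiple imputation by arm, using T0 speed, etiology and age. T0 is taken before allocation, so these inputs exist even for patients who never trained.
- Add a sensitivity analysis for data not missing at random. The model above assumes missing at random and would not by itself remove the bias shown in the working.
- Keep the present set as a further sensitivity analysis, named modified ITT / complete case, and align the Table 4 rationale.
- Do not use an early pre-discharge test as T1 in the primary analysis unless its timing is recorded and accounted for. These patients are still recovering, so a shorter interval brings its own bias if early leaving differs by arm.

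The cost is a small added imputation assumption, some wording, and the effort to obtain T1 from patients who stopped or never started training. No extra patients are needed.

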**Methods/design:**

The GASPAR trial (Gait Adaptation for Stroke Patients with Augmented Reality) is a pragmatic, parallel-arm, single-center, nonblind, superiority randomized control trial in neurorehabilitation. The setting is a rehabilitation clinic in Switzerland. The planned number of participants is 70–100. The intervention uses instrumented treadmills equipped with projectors that display shapes on the walking surface. The principle is that patients must adapt their gait to the image that unfolds in front of them. Specific exercises for gait symmetry, coordination enhancement, and gait agility are provided. The program includes twenty 30-min sessions spanning 4 weeks. The comparator group receives standard treadmill training of a similar frequency and intensity. The main outcome to be measured in the trial is walking speed, which is assessed with the 2-min Walk Test. Moreover, gait parameters are recorded during the gait training sessions. Other outcomes are balance control (Berg Balance Scale) and the fear of falling (Falls Efficacy Scale). The statistical analyses will compare the baseline assessment for each participant (before the intervention) with a post-intervention assessment (taken a few days after the end of the program). Furthermore, a follow-up assessment will take place 3 months after discharge.

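### The stated analyses of walking speed leave out the pre-allocation T0 value as a covariate and rank neither of the two planned tests first

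*Protocol article*

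**What the plan says.** The abstract sets the primary outcome: "The main outcome to be measured in the trial is walking speed, which is assessed with the 2-min Walk Test". The Statistical analysis section puts the comparison on the change scale: "The short-term efficacy of the intervention will be analyzed using the changes between T1 and T0". It states the null hypothesis on the same scale: "As the null hypothesis, we postulate that the change before and after the intervention (T1–T0) will not differ between the two groups". It then names the methods: "We will use simple comparison tests (*t* tests) and multiple regressions". In the regressions, "intervention intensity (number of training sessions), disease etiology, and age will be used as covariates". T0 walking speed is not on that list. The section does not say whether the t test or the regression carries the conclusion, and it lets the interim analysis of 30 participants shape the final methods.

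Two design facts bear on this. T0 precedes randomisation: "After baseline assessments are taken (T0), the sealed envelope is opened to allocate the participant". Etiology is the stratification factor: "stratification is made according to the type of injury: stroke patients, TBI patients, and SCI patients".

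**The concern.** The baseline value of the primary outcome is normally among the strongest predictors of its later value. Here it is collected on every participant before the envelope is opened, so adjusting for it costs nothing and cannot be affected by treatment. Subtracting T0 is not the same as adjusting for it: subtraction fixes the slope of T1 on T0 at 1, whatever the data show. If the true slope differs from 1, the comparison has more variance than it needs, and any chance T0 difference between the arms passes partly into the estimated effect.

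This matters because the sample size is limited by patient flow at one clinic, so precision cannot easily be bought with more patients. The second issue is that two analyses address one null hypothesis with no order between them, in a nonblind trial where an interim look at the outcome data may influence the method. This is not a gap left to an unseen analysis plan: the article itself states the outcome scale, both tests and the covariate list.

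**Working it through.** **Inputs from the protocol article.** Allocation 2:1. Total 70 to 100, which reproduces as a recruitment projection: 35 × 2 = 70 and 50 × 2 = 100 eligible patients over two years. It is not a power-based figure; the Sample size section says the variance of the primary outcome cannot yet be estimated.

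**Assumptions, because the article gives no value.** T0–T1 correlation r; ratio of SDs k = SD(T1)/SD(T0); two-sided 5% level.

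**Precision, equal SDs (k = 1, common SD s).**
- Variance per patient of the change score: 2s²(1−r).
- Variance per patient after baseline adjustment (large samples): s²(1−r²).
- Ratio: (1−r²)/[2(1−r)] = (1+r)/2.

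| r | Variance ratio | Adjusted N matching 70–100 unadjusted | Power if the t test on change has 80% |
|---|---|---|---|
| 0.5 | 0.75 | 52.5–75 | 90% |
| 0.7 | 0.85 | 59.5–85 | 86% |
| 0.9 | 0.95 | 66.5–95 | 82% |

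The N column is 70 and 100 times the ratio.

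**Precision, unequal SDs.** The ratio becomes k²(1−r²)/(1+k²−2rk), and the slope of T1 on T0 is rk.
- r=0.8, k=1.25: 1.5625 × 0.36 = 0.5625, over 1 + 1.5625 − 2 = 0.5625, gives 1.00 (slope 1.00).
- r=0.7, k=1.4: 1.96 × 0.51 = 0.9996, over 1 + 1.96 − 1.96 = 1.00, gives 1.00 (slope 0.98).
- r=0.5, k=0.8: 0.64 × 0.75 = 0.48, over 1 + 0.64 − 0.8 = 0.84, gives 0.57 (slope 0.40).

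Over k from 0.8 to 1.5 and r from 0.5 to 0.9 the ratio ran from 0.57 to 1.00. It equals 1 only where the slope is 1 and never exceeds it, so in large samples adjustment does not lose precision.

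**Chance imbalance.** At N=85 (57:28), the T0 difference between arms has SD √(1/57 + 1/28) = 0.23 in units of the T0 SD. The change-score estimate absorbs (slope − 1) times the observed difference. With an assumed slope of 0.6 and an imbalance of 0.3 SD, that is −0.4 × 0.3 = −0.12 SD. An imbalance this large in either direction is 0.3/0.23 = 1.3 SDs of its distribution, so about 19% of trials would reach it.

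**Two unranked tests.** Simulated under the null at 2:1, counting success if either the t test or the stated regression gives p<0.05, the rejection rate was 5.7–6.1% (N=70 and 100, r=0.5 and 0.8, 8,000 runs each). A separate simulation at N=84, r=0.6 and 12,000 runs gave 5.6%. The excess over 5% is thus 0.6 to 1.1 percentage points. The 5.7–6.1% runs gave the covariates no effect on outcome. Where the two tests agree less, the rate is higher: about 7.8% if the test statistics correlate at 0.8.

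**The case against.** The strongest reply is that nothing here is an error. T0 is taken before allocation, so a t test on change is valid and, averaged over randomisations, unbiased. That stands. A reader might infer that the change-score result would be biased; that is true only conditionally on an observed imbalance, with a slope other than 1.

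The second reply is that the gain cannot be quoted as a firm figure. That also stands. A reader might take (1+r)/2 to promise a fixed saving in patients, but it needs equal SDs and an r that the article does not give. Equal SDs are open to doubt: patients are included once they can walk for 2 minutes, some after not walking at admission, so T0 speeds may be compressed and T1 speeds more spread out. Those are the conditions in which the gain can vanish.

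Third, the t test ignores the stratification factor, but the regression named in the same sentence adjusts for etiology, so the plan does not neglect it altogether.

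Fourth, giving an unadjusted comparison beside an adjusted one is ordinary practice. A reader might infer two rival primary results; the article calls neither analysis primary, and the ranking could be settled in a fuller document. A reader might also put the error rate near 7.5%, but that requires a third, baseline-adjusted model, which this protocol does not plan.

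None of this answers the omission itself: the covariate list is written out, and T0 walking speed is not on it.

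**Conclusion.** The point holds as a matter of efficiency and clarity, not validity. The plan forgoes a covariate it already collects and does not say which of two analyses decides the question. Depending on r and on the ratio of the T1 to the T0 SD, neither of which the article gives, the variance saving lies anywhere from about none to substantial: 25% at r=0.5, 15% at r=0.7 and 5% at r=0.9 if the SDs are equal. These are large-sample figures. Multiplicity from the two planned tests is a minor matter in size, about 5.6–6.1% in the settings simulated. The better reason to name one analysis is that the main estimate is otherwise undefined when the interim data are seen.

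The covariate sentence raises a related problem. Number of training sessions is observed after randomisation and can be affected by treatment. If the arm influences attendance, the planned regression does not estimate the same effect as the t test, so the two cannot be treated as interchangeable.

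**What to change.** Before the 30-participant interim look, name one primary analysis: linear regression of T1 walking speed on arm, T0 walking speed, etiology (three levels, the stratification factor) and age, reporting the adjusted difference between arms with its 95% confidence interval. If the authors prefer to keep the change as the outcome, the arm coefficient is identical once T0 is in the model, so the null hypothesis can stay on the change scale.

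Leave number of training sessions out of this model and state why: it is measured after randomisation and can be affected by treatment. Keep the change-score t test as a sensitivity analysis, labelled as such.

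The cost is a sentence or two in the Statistical analysis section. No new data, visits or patients are needed.

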
The intervention is tailored to the needs and capacity of each participant. For instance, fatigue might make it impossible for a patient to walk for the targeted 25 min, or a frail patient might not make sufficient progress to use the C-Mill after 2 weeks on the Zebris treadmill. Conversely, higher-functioning patients might benefit from C-Mill treatment earlier. The number of intervals performed in each session and the exact training program are documented and taken into account in the statistical analysis.

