### Safety and confidentiality

Fall risks in frail patients are inherent to walking practice. However, the benefits of high-intensity training far outweigh the consequences of an isolated fall. We take several safety measures to mitigate fall risks during the intervention. The participants are constantly supervised by skilled therapists during the interventions and assessments. The participants can use handrails to stabilize their gait during the treadmill intervention. The intervention always begins with the Zebris treadmill, which is equipped with a safety harness; the participants continue with the C-Mill treadmill only if their gaits are sufficiently stabilized.

Other potential burdens may include physical fatigue and muscle pain because of the repetitive practice of exercises. Although this is an inevitable consequence of gait rehabilitation, we will take into account the complaints of the patients by modulating the intensity and frequency of the training sessions. Finally, it cannot be totally excluded that participants in the AR intervention may experience dizziness or vertigo, especially if they have balance disorders. This effect has never been reported in the literature, but we are ready to document and account for this potential adverse event.

Individual subject medical information obtained as a result of this study is considered confidential, and disclosure to third parties is prohibited. During the trial, confidentiality is ensured by utilizing subject identification code numbers. In the final stage of the study, a full anonymization procedure will be conducted to build the final database. All participants are specifically informed about this procedure.

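### The regressions for the between-group effect adjust for number of training sessions, a post-randomisation variable, so the adjusted treatment coefficient can be biased if attendance differs by arm

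*Protocol article*

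**What the plan says.** The Statistical analysis section of the protocol article sets the null hypothesis that "the change before and after the intervention (T1–T0) will not differ between the two groups". It continues: "We will use simple comparison tests (*t* tests) and multiple regressions", and for the regressions "intervention intensity (number of training sessions), disease etiology, and age will be used as covariates". It does not say which analysis decides the question, and it does not label the regression supportive, exploratory or dose-response.

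The same section declares the intention-to-treat principle, applied as follows: "We will analyze all randomized participants for whom the T1 assessment of the primary outcome and at least one training session are available". Table 4 in the Discussion gives the Analysis domain the top pragmatic score, with the rationale "intention-to-treat analysis with all available data".

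On timing, Assignment of interventions and blinding states: "After baseline assessments are taken (T0), the sealed envelope is opened to allocate the participant". On delivery, the Intervention section plans 20 sessions, allows for fatigue and slow progress, and adds: "The number of intervals performed in each session and the exact training program are documented and taken into account in the statistical analysis". Safety and confidentiality says that patients' complaints will be met by "modulating the intensity and frequency of the training sessions".

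**The concern.** A covariate in a model for a randomised comparison should be one that the treatment cannot change. The session count fails that test in two ways.

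- **It may lie on the causal path.** The Background suggests that varied exercises could raise motivation. Safety and confidentiality allows that augmented reality (AR) might cause dizziness or vertigo. Either could change attendance in the AR arm only. If attendance affects recovery, adjusting for it removes that part of the AR effect. Trial objectives lists adherence and tolerance among the things to be assessed, so this is a result of the trial and not a nuisance.
- **It may be a collider.** Attendance also reflects fatigue, complaints and capacity, which plausibly drive recovery as well. If arm and capacity both influence attendance, comparing arms at equal attendance compares patients of unequal capacity, and a difference can appear when AR has no effect.

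At stake is whether the adjusted result for the primary outcome can be read as the effect of assignment to AR. Because neither analysis is named as decisive, the affected model could carry the conclusion.

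**Working it through.** **The plan's own figure.** The only sample-size figure is 70–100, from accrual: 35 × 2 = 70 and 50 × 2 = 100 (etiology rows: 20 + 10 + 5 = 35; 25 + 15 + 10 = 50). It reproduces. It sets the range of N below, but the argument does not depend on it.

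**Inputs from the article.** Allocation 2:1; N 70–100; session count as covariate; allocation before any session.

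**Inputs assumed.** The article gives no SD, no attendance distribution and no relation between attendance and recovery. Two assumed sets were used. U is an unmeasured capacity factor with variance 1, k is the AR-minus-control difference in mean sessions, e and e′ are independent standard normal errors, and the true AR effect is zero.

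- Set A (N = 84, split 56:28; 8,000 runs per k): sessions = 15 + k·arm + 2U + 2e; change = 0.1U + 0.173e′ m/s. The SD of change is √(0.010 + 0.030) = 0.20 m/s.
- Set B (N = 70 and N = 100; 4,000 runs per scenario): sessions = 16 + k·arm + 1.5U + 2.5e; change in SD units = 0.5U + √0.75·e′.

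**Closed form.** With no true effect, the adjusted arm coefficient has expectation −k × (within-arm slope of change on sessions).

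- Set A slope: (2 × 0.1)/(4 + 4) = 0.025 m/s per session, or 0.125 SD.
- Set B slope: (1.5 × 0.5)/(2.25 + 6.25) = 0.088 SD per session.

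| Difference in sessions | A: bias, formula (simulated), m/s | A: type I error | B: size of bias, formula (simulated), SD | B: type I error, N = 70 / N = 100 |
|---|---|---|---|---|
| 0 | 0 | about 5% | 0 | – |
| 0.5 | 0.0125 | about 6% | – | – |
| 1 | 0.025 (0.026) | 8.9% | 0.088 (0.09) | 6.3% / 7.1% |
| 2 | 0.050 (0.050) | 18.6% | 0.176 (0.17–0.18) | 10.4–10.6% / 12.3–12.7% |
| 3 | 0.075 (0.074) | 32.7% | 0.265 (0.26) | 14.9% / 20.8% |

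The sign is opposite to that of the attendance difference: the model penalises the arm that attends more. Without the session covariate, type I error was about 5% in set A and 4.5–5.2% in set B.

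**Hand check of set A, k = 2.** Residual variance is 0.0399 − 0.025² × 8 = 0.0349, so the SD is 0.187. The variance inflation is 1 + 4 × (2/3)(1/3)/8 = 1.111. The standard error is 0.187 × √(1/56 + 1/28) × √1.111 = 0.046. The ratio 0.050/0.046 is about 1.1, which gives roughly 19% rejection at the 5% level, in line with the simulation.

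**Mediation alone.** With no U, a direct effect of 0.50 SD and 0.05 SD gained per session, a difference of ±2 sessions makes the true total effect 0.50 ± 0.10, that is 0.40 or 0.60 SD. The adjusted model returned about 0.50 in both cases; the unadjusted comparison returned 0.40 and 0.60.

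**When attendance is equal.** With k = 0 and a true effect of 0.50, both models returned about 0.50, with or without U. There is no bias.

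Neither set caps the count at the planned 20 or includes etiology and age, so the figures show direction and rough scale only.

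**The case against.** The strongest reply is that a valid randomised comparison is already planned. The unadjusted t test is listed first, addresses the stated null hypothesis directly, and does not involve the session count. That stands. A reader might infer that the trial has no sound test of efficacy, and the article does not support that. What remains is that the regression is given equal footing and no supportive label.

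Second, a reader might infer that the efficacy estimate will be biased. The documents do not show this. Bias in the total effect needs a difference in sessions attended. The Comparator section aims for similar frequency and intensity in both arms, adjustment for complaints applies to everyone, and the AR-specific routes are stated only as possibilities (the article says that dizziness has not been reported in the literature). This limits the likely size, but planned frequency is not attended frequency, and the covariate is the latter.

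Third, the statement in the Intervention section on intervals and training program could be read as putting these too into the between-group model. It does not say so; it may refer to the longitudinal gait analysis or to adherence reporting. It needs clarifying and is not in itself an error.

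Finally, the article says that the interim analysis will guide the final methodology, so the model may change. That makes correction easier, but the covariate is named now and nothing indicates that it would be dropped.

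**Conclusion.** Wrong as written. The article names a post-randomisation variable, open to influence by both arm and prognosis, as a covariate in regressions for the between-group effect. If sessions attended differ by arm, the adjusted coefficient can be biased in either direction and is not an intention-to-treat contrast. If they do not differ, this bias is absent, and the t test is unaffected in either case.

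The size for this trial cannot be derived from the documents. Under the two assumed sets, a 2-session difference gives a bias of about 0.18–0.25 SD and type I error of roughly 10–19%, against about 5% with equal attendance. These values rest entirely on assumed loadings, variances and attendance shifts, and should not be quoted as the trial's error rate.

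**What to change.** - In Statistical analysis, remove number of sessions from every model that estimates the between-group effect. Adjust only for pre-randomisation variables: etiology, age and, if wanted, T0 walking speed.
- State which analysis, the t test or the baseline-adjusted regression, is decisive for the primary outcome.
- Report sessions attended by arm as an adherence result, which also serves the stated objective on adherence.
- In Intervention, state that intervals performed and training program do not enter the between-group efficacy models.
- Label any dose-response analysis exploratory. Arm should not be used there as an instrument for dose: both arms receive treadmill sessions and AR is meant to act through its content as well as through attendance, so the exclusion restriction fails.

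The cost is a sentence or two in each of two sections, with no extra data and no burden on patients.
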